**Table 7.4.1. Classification criteria (NCI-CTC AE 4.0) and recommendations for prevention and treatment**

| Criteria | Definition | Prevention and treatment |
| --- | --- | --- |
| Grade I | SBP 120-139 mmHg, or DBP 80-89 mmHg | Close monitor of BP; Limit sodium intake, and quit smoke and alcohol; Continue to administer anlotinib without dose adjustment. |
| Grade II | SBP 140-159 mmHg, or DBP 90-99 mmHg | Close monitor of BP; Continue to administer anlotinib without dose adjustment; Treatment with antihypertensive drugs, and should not be stopped arbitrarily. |
| Grade III | SBP ≥160 mmHg, or DBP ≥100 mmHg | Suspension of anlotinib; Consider the combination of drugs for hypertension with poor control of monotherapy; Consult a cardiovascular specialist; Close monitor of BP; Continue the drug treatment at a dose reduced by one level with well-controlled blood event |
| Grade IV | Life-threatening (malignant hypertension or  Hypertensive emergencies/persistent neurological deficit) | Immediate and permanent drug discontinuation; Consult a cardiovascular specialist; Aggressive treatment and close monitor of BP and other vital signs |
| Grade V | Death | - |

1. **HFSR**

Patients should avoid mechanical trauma to hands and feet in the treatment, wearing loose-fitting comfortable shoes, softy cotton socks or gloves, and gel inserts, and vigorous exercise which may help limit the reaction; Avoiding direct sunlight on the skin, and using topical emollients or other preparations containing urea or lanolin to protect shin; Avoiding eating hot and spicy food. Treatment of moderate HFSR (if occurs) includes strengthening skin care by mild moisturizer or lubricant to keep the skin clean and moist and avoid secondary infection, pressure, or friction; Topical administration of exfoliating drugs may be administered (such as creams and ointments containing urea, 5% salicylic acid, and corticosteroid lotions), and dissolving the magnesium sulfate in warm water and soaking the affected skin if necessary; Topical antifungals or antibiotics; Appropriately administrating of B vitamins (B1, B6, and riboflavin) and celecoxib. If hyperkeratosis leads to thickened and calloused of foot skin, podiatrists can perform podiatric care to prevent further aggravation and use moisturizing ointment immediately after the pedicure.

The incidence of HFSR decreased with increasing treatment duration in the treatment period. Discontinuing the drug if grade >2 AEs appears three times and tends to worsen, and continue drug treatment if AE resolves to normal or grade 1; If HFSR has no further occurrence, the dose of anlotinib should progressively increase until the standard dose; If grade >2 AEs reoccurs after the resumption of dosing, it is recommended to continue dosing after a dose reducing by one level; If grade 3 of AEs persists or tend to worsen, permanent discontinuation of anlotinib is recommended. Recommendations for the prevention and treatment of anlotinib-associated HFSR can be viewed in **Table 7.4.2** HFSR classification criteria (NCI-CTC AE 4.0) and recommendations for prevention and treatment.

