**Dose Adjustment Criteria**

| **Toxicities graded by NCI** | **Hematological toxicities** |
| --- | --- |
| Grade I | Maintain the original dose (appropriate symptomatic treatment should be provided). |
| Grade II | Maintain the original dose (appropriate symptomatic treatment should be provided). |
| Grade III | Initially, suspend the drug and aggressive symptomatic treatment should be performed, and maintaining the original dose if toxicity restores to grade <II. |
| Grade IV | Initially, suspend drug and aggressive symptomatic treatment should be performed, and downward dose adjustment should be performed if toxicity restores to grade <II. |
|  | **Non-hematological toxicities** |
| Grade I | Maintain the original dose (appropriate symptomatic treatment should be provided). |
| Grade II | Symptomatic treatment and continue drug treatment should be provided. If AE resolves to grade <I within 2 weeks, continue drug treatment; If AE does not improve or aggravate, drug interruption until AE resolves to grade <I and continue drug treatment with original dose level. |
| Grade III | Drug interruption and symptomatic treatment should be provided. If AE resolves to grade <I within 2 weeks, continue drug treatment with the original dose level or at a dose reduced by one level by the investigator's discretion; Drug interruption is recommended if a grade 3 or above adverse reaction occurs. |
| Grade IV | Drug interruption and symptomatic treatment should be provided, and the dose is reduced by one level if AE resolves to grade <I; Drug interruption is recommended if a grade V AE occurs (such as Grade V kidney injury, neurotoxicity, cardiotoxicity, hepatotoxicity, and other life-threatening). |
| **AEs of special interest** | |
| Once hypertensive intracerebral hemorrhage, intracerebral hemorrhage, pulmonary hemorrhage (≥grade II), other hemorrhages (≥ grade III), arterial thrombosis, venous thrombosis (grade IV), Leukoencephalopathy syndrome, and gastrointestinal perforation occur, drug interruption is recommended and aggressive symptomatic treatment should be provided. | |

- 1. **Dose adjustment of gefitinib**

If the patient exhibits intolerable diarrhea (generally associated with dehydration), skin toxic effects, or other AEs caused by gefitinib, briefly discontinuing (up to 42 days) of gefitinib may be performed and then resuming the dose to 250 mg/day for the patient.

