Hypertension is emerging as one of the most common AEs. The [cardiovascular toxicities](https://www.sciencedirect.com/topics/medicine-and-dentistry/cardiovascular-toxicity) panel of the NCI recommends that patients with hypertension at baseline should be diagnosed before VEGF/VEGFR-inhibitor therapy, and patients should have a sustained blood pressure of <140/90 mmHg during the treatment. Blood pressure (BP) should be performed monitored before administration of the drug and especially in the first 2 weeks of treatment (daily monitoring should be performed), and monitoring must continue throughout treatment. Therefore, for patients with hypertension, the antihypertensive drugs should be administered based on individualized principles before receiving anlotinib to achieve early and favorable BP control (BP of ≤140/90 mmHg). However, prophylactic antihypertensive therapy is not recommended for patients with normal BP. Patients should be adequately informed to contact the investigator immediately for guidance when BP is >140/90 mmHg or when symptoms associated with elevated BP occur (e.g., significant headache, dizziness, visual disturbances, etc.). It has been suggested that antihypertensive drugs should be chosen according to the 2010 Chinese guidelines for the management of hypertension, regarding the risk factors for cardiovascular disease in patients. For patients combined with proteinuria, an angiotensin-converting enzyme inhibitor (ACEI) or an angiotensin receptor blocker (ARB) is recommended. A word of caution in drug selection is required that anlotinib is primarily metabolized by the lung CYP3A4 enzyme. Non-dihydropyridine calcium channel blockers (verapamil and diltiazem) can moderate CYP3A4 inhibition and are not recommended for BP control.

If a grade 3-4 increase in BP occurs, antihypertensive treatment or dose modification of this product should be performed under the guidance of the specialist. Drug discontinuation is recommended if the adverse reaction persists. This product should be permanently discontinued in patients who develop a hypertensive crisis. Recommendations for the prevention and treatment of anlotinib-associated hypertension can be viewed in **Table 7.4.1** hypertension classification criteria (NCI-CTC AE 4.0) and recommendations for prevention and treatment.

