**QoL**

The changes in relevant clinical symptoms and objective examination results of patients before and after treatment were observed for scoring, and the scoring results of each domain of the scale were recorded in the eCRF according to the requirements of the quality of life scores. QoL is assessed by the EORTC QLQ-C30 (version 3) and EQ-5D.

- 1. **Safety analysis**
     1. **AEs**
        1. **Definitions of AEs**

AE is defined as any untoward medical occurrence in a patient or clinical investigation subject administered a pharmaceutical product and which does not necessarily have to have a causal relationship with this treatment. Any AEs that occur within 30 days from the initiation of the study drug to the end of treatment in this trial, regardless of whether or not have a causal relationship with this treatment, will be determined as AEs.

Investigators are required to record any AEs in subjects, including the events, AEs-related symptoms, time of occurrence, severity, duration, management, and outcomes.

- - - 1. **AEs grade**

The severity grade of any AEs will be assessed according to the definitions in NCI-CTCAE v4.0. For AEs that are not listed in the table, the following criteria can be referenced.

Grade I is defined as mild; asymptomatic or mild symptoms; clinical or diagnostic observations only; intervention not indicated.

Grade II is defined as moderate; minimal, local, or noninvasive intervention indicated; limiting age-appropriate instrumental activities of daily living (ADL, instrumental ADL refers to preparing meals, shopping for groceries or clothes, using the telephone, managing money, etc).

Grade III is defined as severe or medically significant but not immediately life-threatening; hospitalization or prolongation of hospitalization indicated; disabling; limiting self-care ADL (self-care ADL refers to bathing, dressing and undressing, feeding self, using the toilet, taking medications, and not bedridden).

Grade IV is defined as life-threatening consequences; urgent intervention is indicated.

Grade V is defined as death related to AE.

**Note:** For abnormal AEs or abnormal laboratory test indicators allowed by the inclusion criteria at the time of enrollment, the severity of the AEs and drug adjustments were performed according to the investigator’s discretion.

- - - 1. **Causality to study drugs**

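### Grade IV hypertension: Table 7.4.1 requires a permanent stop of anlotinib, but the general grade IV row in 7.2, read literally, allows restart one dose level lower, and no sentence gives 7.4 precedence (minor safety inconsistency)

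*Protocol*

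**What the plan says.** Two parts of the protocol govern anlotinib after a life-threatening rise in blood pressure.

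**Section 7.4 (event-specific).** Table 7.4.1 defines grade IV hypertension as life-threatening and prescribes "Immediate and permanent drug discontinuation; Consult a cardiovascular specialist". The hypertension text above the table agrees: "This product should be permanently discontinued in patients who develop a hypertensive crisis". The same paragraph also has a broader sentence, "If a grade 3-4 increase in BP occurs, antihypertensive treatment or dose modification of this product should be performed", under specialist guidance.

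**Section 7.2 (general grid, Dose Adjustment Criteria).** For any grade IV non-haematological toxicity the drug is interrupted and treated, and "the dose is reduced by one level if AE resolves to grade <I". The row then adds: "Drug interruption is recommended if a grade V AE occurs (such as Grade V kidney injury", followed by neurotoxicity, cardiotoxicity, hepatotoxicity and other life-threatening events. The special-interest row at the foot of the grid begins "Once hypertensive intracerebral hemorrhage, intracerebral hemorrhage, pulmonary hemorrhage" and goes on to other haemorrhage, thrombosis, leukoencephalopathy and perforation. It does not list hypertension without haemorrhage.

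**Section 10.2 (AE grading).** "Grade IV is defined as life-threatening consequences; urgent intervention is indicated". "Grade V is defined as death related to AE".

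The opening of 7.4 leaves management of anlotinib-related events to the investigator's clinical judgment and offers the event-specific guidance as a reference. It does not say how that guidance ranks against 7.2.

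**The concern.** One document gives two answers to the same question. Under 7.4 a patient who has had malignant hypertension or a hypertensive emergency never receives anlotinib again. Under the grade IV row of 7.2 the same patient may restart at a lower dose once the event has resolved. Section 7.2 presents its grid as the means of keeping dose changes consistent, whereas 7.4 is framed as reference and recommendation, so the wording alone does not tell a site that the stricter rule wins.

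What is at stake is possible re-exposure after a life-threatening event and different handling between centres. No error rate, event count or estimate depends on it.

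**Working it through.** The plan has no figure to reproduce here. The check sets the rules side by side and then bounds how many patients they could concern.

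**Step 1. The rules for a grade IV hypertension event without intracranial haemorrhage.**

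| Source | Action | Restart? |
| --- | --- | --- |
| Table 7.4.1, grade IV | Immediate permanent stop | No |
| 7.4 text, hypertensive crisis | Permanent stop | No |
| 7.2 grid, grade IV non-haematological, first clause | Interrupt, treat | Yes, one level lower after resolution to below grade I |
| 7.2 grid, same row, second clause | Interruption recommended, for grade V events | Not stated |
| 7.2 grid, special-interest row | Not listed | Does not apply |

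The first clause of the 7.2 row is the only one in 7.2 that applies on its literal wording, and it differs from 7.4.

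**Step 2. Does the second clause of the 7.2 row remove the conflict?** Its trigger is grade V, which 10.2 defines as death, so taken literally it cannot govern a restart. Its closing reference to life-threatening events suggests that grade IV was meant. Even then it prescribes interruption, the same term the row uses for the step before a restart, whereas 7.4 says permanent where it means permanent.

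**Step 3. Who could be restarted under 7.2?** Three conditions in the protocol narrow the group:

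- A lower dose level must exist. The ladder in 7.1 is 12, 10, 8 mg, then discontinuation, so a patient already on 8 mg has no lower level to restart at.
- The event must resolve to below grade I. Grade I in Table 7.4.1 starts at 120 mmHg systolic or 80 mmHg diastolic, so the literal threshold is below 120/80. The control target in 7.4 is 140/90, so a patient controlled only to that target does not qualify.
- 7.2 limits suspension for toxicity to 6 weeks per cycle.

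**Step 4. Order of magnitude.** The protocol gives no rate for grade IV hypertension. The nearest figures are:

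- 13.2% grade 3-5 hypertension in a phase III study of anlotinib (section 1.1);
- 2 of 21 patients = 9.5% (exact 95% CI 1.2% to 30.4%) with grade III increased blood pressure at 12 mg (Table 3, which has no grade IV column).

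If the 13.2% carried over to the 155 patients planned for the experimental arm: 155 × 0.132 = 20.5 patients with grade 3-5 hypertension. The share of these at grade IV is unknown. As pure assumptions:

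- 1%: 20.46 × 0.01 = 0.2 patients
- 5%: 20.46 × 0.05 = 1.0 patient
- 10%: 20.46 × 0.10 = 2.0 patients

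These counts come before the three conditions of Step 3, each of which can only lower them.

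**The case against.** The strongest reply is that the safety rule is already stated twice, in the place an investigator treating hypertension would look, and that a general grid followed by event-specific rules is ordinarily read with the specific rule prevailing. That is fair, and it is why most investigators would act correctly. But it is a convention of reading; the protocol does not state it.

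A second reply is that the mislabelled clause in the 7.2 row must concern living patients, since a drug cannot be interrupted after death. The special-interest row also uses interruption for arterial thrombosis, leukoencephalopathy syndrome and gastrointestinal perforation, all of which 7.4 treats as grounds for leaving the study (leukoencephalopathy once imaging confirms it). On this reading the clause points the same way as Table 7.4.1. Much of this stands: the clause was evidently intended as a stop rule. It does not settle the matter, because the same special-interest row also covers grade IV venous thrombosis, for which 7.4 allows a lower-dose restart when the event is asymptomatic. Interruption therefore has no single meaning in the grid.

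Two stronger readings are tempting but unsupported. A reader might infer that the protocol knowingly directs re-exposure after malignant hypertension. The garbled clause and the two explicit permanent-stop statements speak against that. A reader might also count the sentence on grade 3-4 blood pressure increases as a further contradiction within 7.4. The hypertensive-crisis sentence, two sentences later in the same paragraph, already corrects it.

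**Conclusion.** The inconsistency is real and minor. Read as written, the grade IV row of 7.2 permits a restart that 7.4 forbids, and nothing in the protocol ranks the two. It is better described as a missing precedence sentence plus a garbled clause than as two deliberate opposing rules.

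Few if any patients would be affected. The range of 0.2 to 2 in the working rests on a rate from another study and on a grade IV share with no source in the protocol, so it indicates scale only and should not be quoted as an expected count. It also takes the below-grade-I threshold literally. A site that regarded the event as resolved once blood pressure was below 140/90 would reach a restart more easily; 7.4 records hypertension as an adverse event only from grade II, which might encourage that view, but the protocol does not state it.

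It is worth correcting because the event is life-threatening and several centres need one rule.

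**What to change.** Two changes to 7.2:

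1. Add one sentence: where 7.4 gives an event-specific rule, it overrides the general grade rows of the grid, so grade IV hypertension means permanent discontinuation. Confine the sentence to the grade rows. Otherwise it would also decide, by accident, between the ban in 7.2 on returning to a higher dose and the re-escalation that 7.4 allows after hand-foot skin reaction.
2. In the grade IV non-haematological row, change grade V to grade IV for the named toxicities (kidney injury, neurotoxicity, cardiotoxicity, hepatotoxicity), add grade IV hypertension, and replace interruption with permanent discontinuation. Keep the one-level-lower restart for other grade IV non-haematological events.

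The second change should not keep a catch-all for life-threatening events. Section 10.2 describes every grade IV event in those terms, so a catch-all would cancel the restart rule in the same row. Because the repaired clause makes the named grade IV toxicities firm stops, the sponsor's clinicians should confirm the list.

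Narrowing the grade 3-4 sentence in 7.4 to grade 3 is optional tidying.

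The cost is one added sentence and one corrected clause, filed with the ethics committee as section 11.1 requires for any protocol change. Sample size, data collection and analysis stay as they are.

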**Table 7.4.2. HFSR classification criteria (NCI-CTC AE 4.0) and recommendations for prevention and treatment**

| Criteria | Definition | Prevention and treatment |
| --- | --- | --- |
| Grade 1 | Minimal skin changes or dermatitis (e.g., localized erythema, hyperkeratosis, oedema, and painless), but not interfering with daily life | Continuing anlotinib administration without dose adjustment; Treating with topical medication at the first sign of symptoms. |
| Grade 2 | Significant skin changes (flaking, blisters, swelling, and hyperkeratosis) and pain, interfering with daily life and activities. | Continuing anlotinib administration with appropriate dose adjustment; Local drug; Oral B vitamins and celecoxib, and may combine with anti-inflammatory or anti-infective drugs. |
| Grade 3 | Severe skin changes (flaking, blisters, bleeding, ulcers, oedema, and hyperkeratosis) with significant pain and limited personal self-care ability. | Suspension of anlotinib; Analgesic management and topical treatment; Combination of anti-inflammatory or anti-infective drugs; Administering a lower dose of anlotinib if symptoms resolve; Discontinuing anlotinib if symptoms persist and worsen. |

1. **Proteinuria**

When grade >2 proteinuria occurs, the dose of anlotinib is interrupted and awaiting for recovering. If grade 2 or higher proteinuria occurs, continue drug treatment of anlotinib after a dose reducing by one level; if proteinuria persists and worsens, discontinue the drug.

In the event of renal insufficiency or nephrotic syndrome, the drug must be discontinued immediately and aggressive symptomatic treatment must be administered. There is no definitive treatment for proteinuria induced by anti-angiogenic inhibitors, but ACEI and ARB analogues may be administered as appropriate due to their ability in reducing intrarenal tubular pressure and thus proteinuria, as well as reduce possible cardiac AEs. Recommendations for the prevention and treatment of anlotinib-associated proteinuria can be viewed in Table 7.4.2 proteinuria classification criteria (NCI-CTC AE 4.0) and recommendations for prevention and treatment.

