The investigator may destroy the used study drugs (non-state controlled chemicals) and empty boxes/bottles after written notification to the co-organizer without endangering the health of the population. The investigator should keep all study drug-handling records.

These records must document the evidence and quantity of each batch of destroyed drugs, disposal methods (as required by local law), and the person who handled the study drugs.

1. Dose Adjustment and Discontinuation
   1. **Dose adjustment of anlotinib**

The initial dose of anlotinib or placebo is 12 mg/day, and the anlotinib dose can be reduced to 10 mg/day for the first dose and 8 mg/day for the second dose. For patients unable to tolerate a dose of 8 mg/day, anlotinib should be discontinued and gefitinib should be administered alone until PD or intolerable toxicity.

|  | **Study group (anlotinib)** | **Control group (placebo)** |
| --- | --- | --- |
| Initial dose | ■■ 12 mg/day, qd | □□ 12 mg/day, qd |
| First dose reduction | ● 10 mg/day, qd | ○ 10 mg/day, qd |
| Second dose reduction | ■ 8 mg/day, qd | □ 8mg/day, qd |
| Third dose reduction | Discontinuation | Discontinuation |

- 1. **Dosage suspension and reduction**

If dosage suspension caused by drug toxicity has not recovered, the duration of dosage suspension should not exceed 6 weeks per cycle. Follow-up visits will be conducted at least every 1-2 weeks during discontinuation and the drug will be restarted at the original dose or a lower dose level after recovery of toxicity.

The subjects cannot return to the previous dosing pattern after dosage reduction and a maximum of three dose reductions are allowed in anlotinib therapy.

When patients experienced grade 3 hematological toxicities and grade 2 non-hematological toxicities, dosage suspension and reduction are considered; Dosage suspension will be performed in non-hematological toxicities including controllable nausea, vomiting, and fever with a definite cause (below 38°C) until the toxicity became tolerable. Aggressive symptomatic management without dosage suspension and reduction can also be conducted.

- - 1. **Standardization of dose suspension and reduction**

To ensure consistency of dosage adjustment, dosage suspension is performed at the time of dosage adjustments for each cycle. The criteria of dose suspension and reduction are as follows (once the criteria of dosage reduction are met which is considered poorly tolerated, a reduction should be performed).

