**Table 7.4.3. Proteinuria classification criteria (NCI-CTC AE 4.0) and recommendations for prevention and treatment**

| Criteria | Definition | Prevention and treatment |
| --- | --- | --- |
| Grade 1 | Urokinase protein (+) or 24-hour urine protein excretion <1.0 g | Continuing anlotinib administration without dose adjustment |
| Grade 2 | Urokinase protein (++) or 24-hour urine protein excretion of 1.0-3.4 g | Continuing anlotinib administration without dose adjustment; Drug intervention should be considered; Monitor 24-hour urine routine and 24-hour urine protein excretion |
| Grade 3 | 24-hour urine protein excretion >3.4 g | Suspension of anlotinib; Consultation with a nephrologist specialist; Drug intervention should be performed; Dose reduction of anlotinib after recovery of proteinuria to ≤ grade 2; If grade 3 proteinuria still occurs after 2 dose reductions, anlotinib therapy should be permanently discontinued |

1. **Bleeding**

The PT and international normalized ratio (INR) should be closely monitored during the administration of anlotinib to monitor patients for bleeding tendencies and related symptoms; the drug should be interrupted if a grade 3-4 bleeding event occurs. If [upper gastrointestinal bleeding](https://www.sciencedirect.com/science/article/pii/S0025712508000023) occurs, anlotinib must be interrupted and aggressively treated according to clinical protocols should be performed.

1. **Thrombus**

If any arterial thrombosis (e.g., cerebral ischemia, stroke, angina, myocardial infarction) occurs, drug administration should be discontinued immediately and the study should be withdrawn. If symptomatic grade IV venous thrombosis occurs, drug administration should be discontinued in patients, with withdrawal from the study.

For patients with thrombotic symptoms, symptomatic treatment, surgery, or anticoagulant drugs should be scheduled immediately.

For patients with venous thrombosis, the criteria for dose adjustment are as follows:

| **Venous thrombosis** | **Dose adjustment** |
| --- | --- |
| Grade II | Anlotinib is maintained at the original dose level and closely monitored. |

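### Grade 2 proteinuria: the section 7.4 text lowers anlotinib by one level, Table 7.4.3 leaves the dose unchanged, and nothing says which governs

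*Protocol*

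**What the plan says.** The Proteinuria item in section 7.4 first deals with grades above 2: "When grade >2 proteinuria occurs, the dose of anlotinib is interrupted and awaiting for recovering". It then sets a rule that takes in grade 2: "If grade 2 or higher proteinuria occurs, continue drug treatment of anlotinib after a dose reducing by one level". It closes by sending the reader to Table 7.4.2 for the proteinuria criteria. Table 7.4.2 is the hand-foot skin reaction table; the proteinuria criteria are in Table 7.4.3. The grade 2 row there reads: "Continuing anlotinib administration without dose adjustment; Drug intervention should be considered", with urine monitoring added.

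The Dose Adjustment Criteria table in section 7.2 covers grade II non-hematological toxicity in general. It begins: "Symptomatic treatment and continue drug treatment should be provided". A conditional step follows: "If AE does not improve or aggravate, drug interruption until AE resolves to grade <I and continue drug treatment with original dose level". The text of section 7.2 is worded differently: "When patients experienced grade 3 hematological toxicities and grade 2 non-hematological toxicities, dosage suspension and reduction are considered". The same section says of reductions: "The subjects cannot return to the previous dosing pattern after dosage reduction".

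Section 7.1 lists the levels as 12, 10 and 8 mg/day, then discontinuation, with matching steps for placebo. Section 7.4 opens by leaving adverse event management to the investigator, with what follows as a reference.

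**The concern.** A site that follows the section 7.4 text lowers the dose when grade 2 proteinuria appears. A site that follows Table 7.4.3 does not. Both can say they followed the protocol. Section 7.2 gives consistency of dose adjustment as the purpose of its criteria, and this conflict works against that.

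What is at stake is exposure to anlotinib and the meaning of the reported dose-reduction rate. Part of that rate would reflect which page a site read rather than how well the drug was tolerated. Because section 7.2 bars a return to the earlier dose, a reduction made under one reading lasts for the rest of treatment and uses up one of only two lower levels. The wrong table number adds to the difficulty: a reader who follows it reaches the hand-foot skin reaction table, whose grade 2 row does allow dose adjustment.

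**Working it through.** The protocol states no figure to reproduce, so the check compares the instructions and then looks at what a difference means on the dose ladder.

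**Instructions for grade 2 proteinuria**

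| Place | At onset | If it persists or worsens | Dose level |
|---|---|---|---|
| 7.4 text, Proteinuria | Continue after reduction | Discontinue | One level lower |
| Table 7.4.3, grade 2 row | Continue; consider drug intervention; monitor | Not addressed | Unchanged |
| 7.2 general table, grade II non-hematological | Continue with symptomatic treatment | Interrupt, then resume | Unchanged |
| 7.2 text, grade 2 non-hematological | Suspension and reduction to be considered | Not addressed | Left open |

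1. *7.4 text against Table 7.4.3.* Same toxicity, same grade, opposite dose instruction. Both cannot be followed.
2. *General table against Table 7.4.3.* At onset they agree: the drug continues at the same dose. They part only when the event fails to improve or worsens, and even then the general table resumes at the original level.
3. *7.4 text against the general table.* The general table contains no reduction at grade II, so it does not support the 7.4 text.
4. *Grade 3.* Interruption above grade 2, followed by a one-level reduction, can be read in sequence and fits the grade 3 row of Table 7.4.3. The direct clash on dose level is therefore at grade 2.
5. *Precedence.* Nothing says whether a toxicity-specific or a general rule prevails, or whether text or table does.

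**What one level means (section 7.1)**

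- From 12 to 10 mg/day: (12 − 10)/12 = 16.7% lower daily dose.
- From 10 to 8 mg/day: (10 − 8)/10 = 20% lower.
- From 8 mg/day: the next step listed is discontinuation. For a patient already at 8 mg/day, the two readings differ between stopping anlotinib and continuing it.

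**How common the toxicity is (Table 3, anlotinib 12 mg, N = 21)**

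- Albuminuria, grade I/II, whole study: 14/21 = 66.7%, matching the stated 67%. This is the highest count for any single event in that column; the next are elevated total cholesterol (13) and hypothyroidism (12).
- First two cycles: 5/21 = 23.8%. Grade III: none.
- Grades I and II are pooled, so the grade 2 frequency cannot be extracted.

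**The case against.** The strongest reply is that section 7.4 is guidance. It leaves management to the investigator, and section 7.2 itself only asks that suspension and reduction be considered at grade 2, so some variation is intended. That stands in part: it lowers the force of either sentence. It does not make two opposite statements about one grade compatible, and section 7.2 also says that a reduction should be made once its criteria are met.

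A second reply is that the proteinuria sentence was meant for recurrence after interruption, as in the parallel hand-foot skin reaction text, which speaks of recurrence after dosing resumes. This is plausible and would affect fewer patients. But the sentence as written speaks of occurrence, and a grade 2 recurrence would still be handled differently in Table 7.4.3.

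A third concerns permanence: the hand-foot skin reaction text does provide for raising the dose again. The proteinuria text has no such provision, so for this toxicity the bar in section 7.2 applies as written.

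Three stronger readings might be inferred, and the protocol does not support them.

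- *That there are three mutually incompatible rules.* The general table interrupts only if the event does not improve or worsens. At onset it agrees with Table 7.4.3. On dose level the direct conflict is between two instructions: reduce, or leave unchanged.
- *That up to 67% of the experimental arm is affected.* The 14 of 21 pools grades I and II in a phase I sample, with an exact 95% confidence interval of 43% to 85%. It is neither a grade 2 figure nor a ceiling for a first-line combination with gefitinib.
- *That the PFS comparison is biased or patients are put at risk.* Nothing in the protocol demonstrates either. The same dose steps apply to blinded placebo, so the ambiguity creates no evident difference in how the arms are handled.

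**Conclusion.** The point holds as an internal contradiction between the section 7.4 text and the grade 2 row of Table 7.4.3. It is made less clear by the differing wording in section 7.2 and by a wrong table number. The supported consequence is inconsistent anlotinib dosing and a dose-reduction rate that is difficult to interpret. For a patient starting at 12 mg/day the two readings differ by 2 mg/day, or 16.7%, without a return. The number of patients affected is unknown: albuminuria was common at 12 mg, but the protocol does not give the grade 2 share.

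This rests on reading the sentences as written, and on there being no precedence rule in the protocol. It should be corrected, but it does not call the primary test into question, and it implies no view on which action is clinically right.

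**What to change.** Reconcile four places so that grade 2 proteinuria has one stated action, chosen by the clinical team: the Proteinuria text in section 7.4, the grade 2 row of Table 7.4.3, the grade II non-hematological row of the Dose Adjustment Criteria table, and the sentence on grade 2 non-hematological toxicity in section 7.2. If the section 7.4 sentence was meant for recurrence, say so. State whether the toxicity-specific or the general table governs when they differ. Correct the cross-reference in the Proteinuria text from Table 7.4.2 to Table 7.4.3.

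The cost is a change of protocol wording and a notification to sites.
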